### 5.3 Preclinical safety data

Not applicable.

## 6. PHARMACEUTICAL PARTICULARS

### 6.1 List of excipients

Maize starch, sodium bicarbonate, croscarmellose sodium, white beeswax, titanium dioxide (E 171), ethylcellulose, glycerol monooleate, polysorbate 80, povidone, sucrose, anhydrous colloidal silica, magnesium stearate, talc.

### 6.2 Incompatibility

Not applicable.

### 6.3 Shelf-life

3 years.

### 6.4 Special precautions for storage

There are no special precautions for storage.

### 6.5 Nature and contents of container

Heat-formed blister packs (PVC plus aluminium foil).

### 6.6 Instructions for use and handling

(cf. 4.2 Posology and method of administration).

## 7. MARKETING AUTHORIZATION HOLDER

LES LABORATOIRES SERVIER  
[name]  
[name]

## 8. NUMBER(S) IN THE COMMUNITY REGISTER OF MEDICINAL PRODUCTS

France: 317 557.9 (30 tablets)  
317 559.1 (100 tablets)

## **9. DATE OF FIRST AUTHORISATION/RENEWAL OF THE AUTHORISATION**

16-07-1974  
modification: 22-04-1987

## **10. DATE OF REVISION OF THE TEXT**

02-10-2002

## **Appendix 7: Concomitant medications**

### **DRUGS NOT ALLOWED**

- Any sulfonylurea other than the one received at selection, and to be prescribed throughout the study at the same dosage unless a decrease in the sulfonylurea dose is judged necessary by the investigator (e.g. severe or multiple hypoglycaemic episode).
- Short acting insulin secretagogues (such as repaglinide or nateglinide).
- Insulin (contraindicated with pioglitazone).
- Biguanides (such as metformin).
- $\alpha$ -glucosidase inhibitors.
- Other thiazolidinedione (Rosaglitazone).
- Drugs contraindicated with sulfonylureas: Miconazole – systemic route, oral gel – is an absolute contraindication (please refer to the Summary of Product Characteristics of the prescribed sulfonylurea).
- Oral injected corticosteroids in chronic use (see “Drugs allowed for short term use in exceptional cases” below).

### **DRUGS ONLY ALLOWED IN CHRONIC USE**

- Usual concomitant medications are authorised if resulting in a well controlled and stabilised pathology. Their dosage should remain stable throughout the study as far as possible
- Weight lowering agents and lipid lowering agents are authorised only if they have been taken for at least 3 months before selection and can be taken throughout the study at stable daily dose. Starting lipid lowering drugs is allowed from W8.

### **DRUGS ONLY ALLOWED FOR SHORT TERM USE IN EXCEPTIONAL CASES**

Oral and injected corticosteroids are accepted only if needed for a duration of less than 10 days and at a distance of at least one month from the forthcoming evaluation visit. Oral and injected corticosteroids are not allowed if chronically used.

Insulin is allowed for short term treatment (< 7 days).

### **SPECIAL WARNINGS AND SPECIAL PRECAUTIONS FOR USE**

NSAIDs: Since their combination with Pioglitazone is associated with fluid retention, their use should be considered with the greatest precautions.

## Appendix 8: Hypoglycaemia

### 1) Patient information

The investigator will inform the patient on trigger factors of hypoglycaemia, and on symptoms suggestive of hypoglycaemia.

A list of symptoms indicative of hypoglycaemia is given in table 1. A symptomatic hypoglycaemic episode could also be suspected on the acute onset of unusual symptoms on the judgement of the investigator.

Table 1: Symptoms indicative of hypoglycaemia

|                                                               |                                                   |
|---------------------------------------------------------------|---------------------------------------------------|
|  Confusion                            |  Difficulty concentrating |
|  Sweating                             |  Unsteadiness             |
|  Unexplained behaviour or mood change |  Visual disturbance       |
|  Drowsiness                           |  Hunger                   |
|  Weakness                             |  Pallor                   |
|  Lightheadedness                      |  Nausea                   |
|  Dizziness                            |  Incoordination,          |
|  Difficulty speaking                  |  Tremor                   |
|  Pounding heart                       |  Headache                 |

Table 2: Trigger factors of hypoglycaemia

|                                                                                                                                                                                                                                                                                    |
|------------------------------------------------------------------------------------------------------------------------------------------------------------------------------------------------------------------------------------------------------------------------------------|
|  missed meal or meal without carbohydrates,
 unusual physical exercise,
 absorption of alcohol without food,
 new concomitant treatment
 other |
|------------------------------------------------------------------------------------------------------------------------------------------------------------------------------------------------------------------------------------------------------------------------------------|

### 2) Management of hypoglycaemia

#### By the patient:

Hypoglycaemia must be immediately treated by sufficient sugar intake, i.e. equivalent to 10 g of glucose per os or 9 g of glucose IV.

The patient should be encouraged to report any severe and/or multiple hypoglycaemic episodes to the investigator, even outside planned study visits.

He/she should be encouraged to fill in his/her diary card with as many details as possible, particularly:

- Date and time of onset
- Description of the symptoms
- Management of the episode (sugar intake, other...)
- Duration of symptoms after sugar intake

**By the investigator:**

The symptomatic hypoglycaemic episodes are considered:

- Mild: if the symptoms did not interfere with usual activities,
- Moderate: if the symptoms transiently interfered with usual activities,
- Severe: defined as symptomatic episode requiring external assistance due to severe impairment in consciousness or behavior.

In case of severe or multiple (> 3 episodes per month) hypoglycaemic episodes, an adjustment in the antidiabetic treatment may be judged necessary by the investigator: the sulfonylurea dose can be decreased and in the same time glucose or glucagon quickly administrated.

In all cases, the investigator will reinforce advice on hypoglycaemia and particularly triggers factors to be avoided.

**3) Reporting of hypoglycaemia**

In the case report form, the investigator will fill in the specific form “Record of suspected hypoglycaemia” in the CRF:

- date/time of onset,
- measures taken by the patient,
- duration of symptoms after sugar intake,
- severity of the episode (see 2),
- any adjustment in the antidiabetic treatment (see 2).

This form should only be filled in for episodes suggestive of hypoglycaemia. All the other adverse events should be reported in the Adverse Events Form.

**In case of severe hypoglycaemic episode, the investigator will also follow the procedure for serious adverse events described in section 12.3.1.3.**

## **Appendix 9: Blood sampling in case of overdose**

### **Sample treatment**

2 mL blood samples will be collected in dry tubes.

The blood will be **immediately** separated into plasma by centrifugation (10 mn, at 3500 rpm at + 4° C) and will be **immediately** stabilized by adding sodium fluoride (50 µL of a 40 mg/mL solution/mL plasma).

Plasma will be separated and divided into 2 aliquots in 2 tubes for determination of S 780 and its metabolites (aliquots n°1 and n°2). Each aliquot will be clearly identified with the following information: protocol number, centre number, patient identification, birth date, time of sampling, aliquot number (1 or 2).

Each sample will then be rapidly deep frozen and stored at – 20°C. These samples can be stored at -20°C for a maximum of one week before transfer to the central laboratory.

### **Samples transfer**

Aliquot n°1 and n°2 will be sent frozen in dry ice by special delivery to the central laboratory. The procedure will be specified in the central laboratory manual.

## Appendix 10: Procedure to be followed in case of suspicion of heart failure

All along the study, in case of occurrence of symptoms suggestive of heart failure (dyspnea, dyspnea with exertion, orthopnea, tachycardia, paroxysmal nocturnal dyspnea, unexplained cough, fatigue, oedemas) a **physical examination** should be performed to determine if there are signs of congestive heart failure (jugular venous distension, S3 gallop, pulmonary rales...).

In case of suspicion of heart failure the investigator should prescribe as soon as possible and prior to any specific treatment, **NT-proBNP and serum creatinine sampling**. If **NT-proBNP  $\leq$  300 pg/mL heart failure can be ruled out** and the investigator may consider another diagnosis.

**If NT-proBNP > 300 pg/mL, a full cardiological examination** should be prescribed as soon as possible with:

- ECG: to assess changes from baseline.
- Doppler Echocardiography: to assess left ventricular filling pressure and pulmonary pressure.

The patient file should be transmitted as soon as possible to the **Adjudication Committee for assessment**.

**If heart failure is confirmed:**

- **Study treatment should be discontinued** (see paragraphe 9.6.1)
- Specific treatment for cardiac heart failure should be started under medical control. According to the level of emergency, the patient will be hospitalized or treated under outpatient medical care.
- **Patient will be controlled two weeks later** by his/her research doctor in order to evaluate his/her clinical medical state.

[figure not shown]

\*All files with NT-proBNP > 300 pg/mL will be submitted to the Adjudication Committee

## Appendix 11: Procedure to be followed in case of oedema

If oedema is present at selection visit, description should be performed and aetiology should be precised and reported in the part Medical History of the CRF.

All along the study, in case of occurrence of oedema the investigator should proceed as follow (record in CRF):

- **Describe** clinical symptoms.
- **Investigate** for signs of heart failure (eg, jugular venous distension, S3 gallop, pulmonary rales).
- **Clarify** the aetiology of oedema (refer table bellow).

In case of oedema with hydrosodic retention, the investigator should perform as soon as possible and **prior to any specific treatment NT-proBNP and serum creatinine sampling.**

In case of oedema requiring emergency treatment, the patient should be hospitalized. Hospital report as well as any test performed during hospitalisation will be considered by the Adjudication Committee to analyse the case.

In case of oedema associated with heart failure see appendix 10: procedure to be followed in case of heart failure.

If oedema is moderate, treatment will only be started after biological tests performed and, if applicable, after cardiac examination by a cardiologist.

### Description of oedema:

#### Clinical symptoms:

- |                                                                           |                                          |
|---------------------------------------------------------------------------|------------------------------------------|
|  Depressible                                      |  Not depressible |
|  Bilateral                                        |  Unilateral      |
|  Painless                                         |  Painful         |
|  Gravity oedema                                   |                                          |
|  Non inflammatory                                 |  Inflammatory    |
|  Increase of body weight $\geq$ 2kg within a week |                                          |

#### Clinical symptoms, if any, of heart failure:

- ☐ Jugular venous distension
- ☐ Pulmonary rales
- ☐ S3 gallop
- ☐ Hepatomegalia

#### Aetiology of oedema :

- ☐ Venous retention
- ☐ Lymphatic retention
- ☐ Renal aetiology
- ☐ Pre-menstrual oedema
- ☐ Calcium channel blockers treatment
- ☐ Vasodilators
- ☐ NSAID
- ☐ Hypothyroidism
- ☐ Other:

- ☐ Heart failure suspected

In case of hydrosodic oedema (not including pre-menstrual oedema) tests should be performed :

- **NT-proBNP dosage**
- **Serum creatinine**

- If NT-proBNP is  $\leq$  300 pg/mL, you can consider another diagnostic than cardiac insufficiency.
- If NT-proBNP is  $>$  300 pg/mL, patient should be prescribed **a full cardiac examination by a cardiologist.**

## Appendix 12: Procedure to be followed in case of anaemia

An anaemia discovered during the study is diagnosed by the association of both:

- **Haemoglobin level < 12g/dL in men and < 11g/dL in women**
- AND**
- **Decrease of haemoglobin > 1.5g/dL in men and > 1g/dL in women**

The blood test will include erythrocytary indexes, haptoglobin and ferritin to clarify the aetiology of anaemia.

**If anaemia is confirmed, the patient will stop his/her treatment** (see paragraph 9.6.1), and usual investigations should be performed by the investigator in order to treat the patient. The investigator should also report the anaemia as adverse event (adverse event form should be completed).

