### 9.4. Non-inclusion criteria

- Presence of non-selection criteria after the clinical and biological examinations performed since the visit ASSE and particularly if blood pressure is above the upper limit at both the selection and the inclusion visit, the patient must not be included (see section 9.2).
- Patient unable to comply with the study treatment particularly if compliance assessed at the W0 visit of run-in placebo capsules or run-in placebo tablets is  $> 120\%$  or  $< 80\%$ .

- Left Ventricular Ejection Fraction (LVEF) < 40% and any major cardiac pathology discovered at echocardiography according to local assessment (see appendix 16).
- Abnormal biological results:
  - o ALAT > 2.5 times the Upper Limit Normal (ULN) value.
  - o Haemoglobin level < 12 g/dL in men and < 11 g/dL in women.
  - o Creatinine clearance < 30 mL/min according to the Cockcroft and Gault formula (see appendix 15).
  - o Triglycerides > 4 g/L (4,6 mmol/L.)
- Unauthorised concomitant treatments (see appendix 7).

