### 9.6. Participant withdrawal criteria

#### 9.6.1. Withdrawal criteria

Premature discontinuation of treatment, does not necessarily mean that the patient prematurely stops the participation in the study. Information to be collected during the follow-up of these participants is given in section 9.6.2. These follow-up modalities are used to insure the efficacy and safety evaluation of all patients who received the study drug.

The reasons for premature discontinuation of treatment are:

- **Adverse events or any condition incompatible with continuation of either treatment** according to the judgement of the investigator or for which the continuation of the study is recommended (refer to the investigator's brochure of benfluorex and pioglitazone monography in appendices 5 and 6). These include:
  - **Hypoglycaemia incompatible with treatment continuation**, e.g. occurrence of one episode of severe hypoglycaemia or repeated non severe hypoglycaemia (> 3 per month) if the sulfonylurea dose can not be decreased anymore.
  - **ALAT increase > 3 times the ULN value**, after 2 consecutive tests performed in 7 days apart (see appendix 5).
  - **Cardiac failure** (see appendix 10).
  - **Clinically significant anaemia** defined by an haemoglobin level < 12g/dL in men and < 11g/dL in women and a decrease  $\geq 1.5$  g/dL in men and  $\geq 1$  g/dL in women (see appendix 12).

- **Major deviation to protocol incompatible with continuation of either treatment** (including pregnancy).
- **Treatment failure (lack of efficacy) defined as uncontrolled metabolic state with:**
  - **HbA1c > 9.5% at W16 or HbA1c > 9% at W28 or W40** unless increase to dose level B is still possible. If external factors (poor compliance, change of diet and lifestyle, occurrence of infectious or inflammatory disease, intake of corticosteroids) are detected, the investigator will reinforce diet advice and recommendations about treatment intake and/or study protocol compliance. At the following study visit, if the HbA1c is still > 9% the study treatment will be stopped.
  - **or hyperglycaemia** unexplained by external factors and confirmed by either:
    - o clinical symptoms (thirst, polyuria,...) and FPG  $\geq$  13.9 mmol/L
    - o or no symptom and FPG  $\geq$  13.9 mmol/L at 2 consecutive measurements separated by an interval of 2 to 4 weeks.
- **Any medical event requiring administration of an unauthorised concomitant treatment** (see paragraph 10.3).

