- **Non-medical reason** (to be carefully described).
- **Lost to follow-up:** when the investigator has no news of the participant, he/she must make every effort to contact him/her, to establish the reason for the discontinuation of treatment, and to suggest the participant for coming to an end-of-study visit. If all these attempts to contact the participant fail, the investigator can then declare the participant “lost to follow-up”. The investigator should document all these attempts in the corresponding medical file.

In cases corresponding to the above, the study treatment will be stopped and the investigator will be responsible to take all the appropriate therapeutic measures to control the glycaemic level.

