**The following safety laboratory assessments will be performed:**

- Standard haematology: red blood cell count, red blood cell indexes, white blood cell count, differential white blood cell count, blood smears, platelet count. They will be assessed at each visit and in case of premature discontinuation.
- Biochemistry
  - o Total proteins, creatinine, albumin, sodium, potassium, chlorides calcium, total bilirubin, alkaline phosphatase. They will be assessed at W0, W28 and W52 and in case of premature discontinuation.
  - o Lactic acid and uric acid will be assessed at W0, W52 and in case of premature discontinuation.
- NT-proBNP will be assessed centrally at W0, W28, W52, in case of premature discontinuation and in case of oedema (to evaluate an underlying heart failure).

**Liver enzymes** (ALAT, ASAT,  $\gamma$ -GT) will be assessed at W0, W4, W8, W16, W28, W40, W52 and in case of premature discontinuation.

- **If ALAT level is > 2.5 times the upper normal limit prior to inclusion, the patient should not be included.**
- **If ALAT level is > 3 times the upper normal limit after inclusion,** a re-test should be performed within 7 days. If the value remains 3 times the normal upper limit, the study treatment will be stopped and the patient withdrawn.
- **In case of unexplained symptoms suggestive of hepatic disease** (nausea, vomiting, abdominal pain, fatigue, loss of appetite, jaundice, dark urines), complete liver function tests should be performed. Until the results are obtained, the decision to maintain study treatment will relay on clinical judgement. In case of jaundice, the study treatment will be discontinued.

**Haemoglobin and haematocrit will be assessed** at every visit and in case of premature discontinuation.

- **If, at inclusion, haemoglobin level is < 12g/dL in men and < 11g/dL in women, the patient should not be included.**
- **If, after inclusion, clinically significant anaemia** is detected, see appendix 12.

The results (with the clinical assessment of the investigator) will be included in the CRF and one copy kept in the patient file. The investigator will report in the adverse event section of the CRF the abnormal biological parameters **only** if considered as clinically significant and not already reported/considered as pre-existing conditions without aggravation.

- **Body weight, heart rate, blood pressure, ECG and echocardiography:**

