#### 12.3.1.1.2. Recording methods

Adverse events must be documented on an "Adverse event" form ("Initial information" page and if necessary "Additional information" pages) according to the general instructions for completion appended in the CRF

Some sections of the page must always be completed, whether or not the event requires immediate notification. Further sections must be completed only when the event requires immediate notification.

In the case of disease progressing by episodes (chronic disease):

- if the disease is known when the participant enters the study, only worsening (increased frequency and/or intensity of the episodes/attacks) will be documented as an adverse event,
- if the disease is detected during the study and if repeated episodes enable diagnosis of a chronic disease, the episodes will be grouped on the same page "Adverse event – Initial information" which will clearly describe the diagnosis.

For the following adverse events, additional information will be requested and specific procedure should be followed:

- **Hypoglycaemia:** the episodes of hypoglycaemia will be recorded on the « Suspected hypoglycaemia form ». See specific procedure Appendix 8.
- **Oedemas:** See specific procedure Appendix 11.
- **Heart failure:** See specific procedure Appendix 10.
- **Anaemia:** See specific procedure Appendix 12.

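### The anaemia stopping rule uses an inclusive haemoglobin fall in Section 9.6.1 (1.5/1 g/dL or more) and a strict one in Appendix 12 (more than 1.5/1 g/dL)

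*Protocol*

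**What the plan says.** Section 9.6.1 of the protocol lists clinically significant anaemia among the reasons for premature discontinuation of treatment. It is "defined by an haemoglobin level < 12g/dL in men and < 11g/dL in women and a decrease" that is greater than or equal to 1.5 g/dL in men and greater than or equal to 1 g/dL in women, and the sentence ends by pointing to Appendix 12 ("g/dL in women (see appendix 12"). The section closes with an order covering every listed reason: "In cases corresponding to the above, the study treatment will be stopped".

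Appendix 12 gives its own diagnosis. It requires two things together: the same haemoglobin levels, and "Decrease of haemoglobin > 1.5g/dL in men and > 1g/dL in women". It then asks for red cell indices, haptoglobin and ferritin, and says: "If anaemia is confirmed, the patient will stop his/her treatment", with a reference back to Section 9.6.1. It also asks for an adverse event report.

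Two other places send the investigator to the appendix without giving a threshold. Section 12.2 says that if clinically significant anaemia "is detected, see appendix 12". Section 12.3.1.1.2 says, for anaemia, "See specific procedure Appendix 12".

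**The concern.** One stopping rule has two definitions, differing in the inequality applied to the fall. Section 9.6.1 includes the limit and Appendix 12 excludes it. No sentence ranks the two.

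Three places in the protocol lead to Appendix 12, so the narrower version is likely to be the one open when the decision is made. An investigator working from it could keep a patient on treatment whom Section 9.6.1 requires to stop. The appendix would also not call for the haptoglobin and ferritin tests or the adverse event report in that patient. A monitor could not say with certainty whether continuing was a protocol deviation.

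The subject is relevant here. Section 6 names anaemia with fluid retention as a possible effect of the comparator's class, and the pioglitazone product summary in Appendix 5 (section 4.4, Haematology) reports a 4% relative reduction in mean haemoglobin.

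**Working it through.** **Step 1. The two rules side by side.**

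| | Level, men / women | Fall, men / women |
|---|---|---|
| Section 9.6.1 | < 12 / < 11 g/dL | ≥ 1.5 / ≥ 1 g/dL |
| Appendix 12 | < 12 / < 11 g/dL | > 1.5 / > 1 g/dL |

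Both conditions must hold in each rule. The levels are identical, so the rules can differ only when the fall equals the limit exactly.

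**Step 2. Can such a patient occur?** Section 9.4 bars entry with "Haemoglobin level < 12 g/dL in men and < 11 g/dL in women", so men enter at 12.0 g/dL or more and women at 11.0 or more. Assume reporting to 0.1 g/dL and a fall counted from W0; the protocol states neither.

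- Men: the follow-up value must be 11.9 or lower, so the entry value is at most 11.9 + 1.5 = 13.4. Affected entry range: 12.0 to 13.4 g/dL.
- Women: the follow-up value must be 10.9 or lower, so the entry value is at most 10.9 + 1.0 = 11.9. Affected entry range: 11.0 to 11.9 g/dL.

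Examples:

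- Man, 13.4 to 11.9: 11.9 < 12 and the fall is 1.5. Since 1.5 ≥ 1.5, Section 9.6.1 stops treatment. Since 1.5 is not > 1.5, Appendix 12 does not.
- Woman, 11.9 to 10.9: 10.9 < 11 and the fall is 1.0. Section 9.6.1 stops treatment; Appendix 12 does not.

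**Step 3. How often?** The protocol gives no haemoglobin distribution, so this rests on assumptions:

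- baseline mean 14.6 (SD 1.2) g/dL in men and 13.2 (SD 1.1) in women, truncated at the entry limits;
- SD of change 0.6, 0.8 or 1.0 g/dL;
- equal numbers of men and women;
- mean change zero on benfluorex;
- mean change on pioglitazone either zero or the 4% relative fall from Appendix 5.

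Allocation is 1:1 (Section 8.3). Baseline and follow-up values were simulated (4 million draws per sex and scenario) and rounded to 0.1 g/dL. The counts are patients exactly on the limit / all patients meeting the Section 9.6.1 definition, per 1000 at one visit, averaged over the sexes.

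| SD of change | No mean change | 4% fall (pioglitazone arm) | Both arms, 4% fall on pioglitazone only |
|---|---|---|---|
| 0.6 | 1.2 / 5.3 | 3.8 / 26.2 | 2.5 / 15.8 |
| 0.8 | 1.9 / 15.6 | 4.1 / 48.0 | 3.0 / 31.8 |
| 1.0 | 2.4 / 30.4 | 3.9 / 71.6 | 3.1 / 51.0 |

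The last column is the average of the two before it; for SD 0.6, (1.2 + 3.8) / 2 = 2.5. If neither arm has a mean change, the first results column applies to the whole trial. The trial-wide range is therefore 1.2 to 3.1 per 1000 on the limit, out of about 5 to 51 per 1000 who meet the Section 9.6.1 definition.

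Moving both baseline means by 0.5 g/dL either way gives 1.2 to 5.5 per 1000 with the 4% fall on pioglitazone and 0.5 to 4.2 with no fall in either arm, so 0.5 to 5.5 overall. A repeat of the simulation agreed with these figures to within about 0.1 per 1000 on the limit.

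**The case against.** The strongest reply is that the two texts can be applied together. Section 9.6.1 is the governing list of reasons to stop, and Appendix 12 is a procedure that refers the stop back to it. Section 12.2 sends the reader to the appendix once clinically significant anaemia has been found, and only Section 9.6.1 defines that term. On this reading Section 9.6.1 decides and the appendix describes what follows; stopping at the limit breaches neither text. That is a fair reading, but the protocol does not state it. Appendix 12 sets out a complete diagnosis of its own rather than taking over the one in Section 9.6.1.

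The second reply is that little depends on it, and this stands. A fall 0.1 g/dL to either side of the limit gets the same answer from both rules. Haemoglobin is measured at every visit, red cell indices are already routine, Section 9.6.1 lets the investigator stop for any condition judged incompatible with treatment, and Sections 12.2 and 12.3.1.1.1 require an adverse event report for a laboratory finding judged clinically relevant. What the appendix alone adds is haptoglobin, ferritin and an automatic report.

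Third, the frequencies are mostly assumption. Baseline SD and sex split were not varied, and the figures are per visit, not patients affected over the whole study. That limits the estimate of size; it does not bear on the mismatch in the text.

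Finally, a sign could have lost its bar when the PDF was read. This is unlikely, because inclusive signs survive in neighbouring appendices.

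**Conclusion.** The concern holds. A safety stopping threshold is defined in two ways in current text, and a patient whose fall lands exactly on the limit must stop under one definition and is not anaemic under the other. That conclusion rests on the wording alone.

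Its practical size is small: roughly 1 to 3 patients per 1000 at any one visit, or 0.5 to 5.5 with shifted baselines, if haemoglobin is reported to 0.1 g/dL, the fall is counted from W0 and the assumed distributions are about right. Existing safeguards would catch some of these patients. The primary HbA1c analysis does not depend on the rule, nor does the description of haemoglobin by group planned in Section 14.1.4. This is a correction worth making when the protocol is next amended, not a threat to the trial's conclusions.

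**What to change.** In Appendix 12, change the second diagnostic line so that the fall reads ≥ 1.5 g/dL in men and ≥ 1 g/dL in women. This adopts the more protective rule already in Section 9.6.1, which needs no change. The cost is two operators on one line, with no added measurement, patient or analysis.
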